## Abstract

**Background:**

It is well documented that individuals with Alcohol Use Disorder (AUD) respond well during evidence-based psychological treatment, but also that a large proportion relapses when discharged from treatment and confronted with alcohol in real life. Cue Exposure Treatment (CET) focuses on exposing individuals to alcohol cues in order to reduce cravings as well as the likelihood of relapse.

The aims of the study are: 1) to investigate whether CET aftercare delivered via a smartphone or in group sessions increases the effect of Cognitive Behavioural Treatment in groups of alcohol dependent individuals; 2) to investigate whether CET as a smartphone application is as or more effective than CET group therapy, and 3) to investigate whether CET as a smartphone application is more cost-effective than CET group aftercare and Aftercare as Usual.

**Design and methods:**

The study will be implemented as an investigator-blinded randomized controlled trial. A total of 300 consecutively enrolled alcohol use disorder individuals recruited from an alcohol outpatient clinic will be randomized into one of the three following aftercare groups after concluding primary treatment: (1) CET as a smartphone application; (2) CET as group therapy, and (3) Aftercare as Usual. It is hypothesized that the two experimental groups will achieve better treatment outcomes compared to the control group (3).

**Discussion:**

Individuals in the CET groups are given the opportunity to practise coping strategies during exposure to alcohol stimuli before being unavoidably confronted with alcohol and associated stimuli in real life. Thus, CET may help prevent patients from relapsing after concluding treatment, and in the long term. Moreover, the CET application has the potential to improve AUD treatment and continuing care by offering psychological treatment whenever and wherever the patient finds it convenient.

**Trial registration:**

ClinicalTrials.gov ID: NCT02298751

Registration date: 6 November 2014

## Background

Alcohol Use Disorder (AUD) is a widespread problem in Denmark*,* and it is a well-known fact that AUD leads to a substantial number of contacts with the treatment system, which constitutes a substantial burden on the healthcare system [1]. Individuals with AUD respond relatively well during evidence-based psychological treatment, but a large number of patients relapse when discharged from treatment and confronted with alcohol in real life [2, 3]. During evidence-based psychological alcohol treatment, in particular when applying Cognitive Behavioural Therapy (CBT), patients learn methods to help them identify high-risk situations for relapse. They also learn coping strategies for avoiding or confronting alcohol and associated high-risk situations [4–8]. However, patients are supposed to learn this by talking about what to do, not by actually being exposed to alcohol and practicing the strategies in vivo, as CBT is delivered when specifically targeting AUD. For the patient, the real challenge is to make use of coping strategies in real life outside the treatment setting; to actually use the strategies before or in the situation in question. All too often, the patient relapses when exposed to alcohol and associated stimuli and can afterwards only analyse and describe what went wrong. In other words, the challenge is to prepare the patient for his confrontation with alcohol, given that avoiding alcohol-related situations in a Danish context is almost impossible, and to provide the patient with strategies that can be used before he/she starts to drink, in order to prevent a relapse.

A reasonable means to achieve this goal is to teach the patients how to apply coping strategies to regain control over their alcohol cravings in their daily confrontations with alcohol and associated stimuli before the end of their contact with the treatment institution. Cue Exposure Therapy (CET) is a behavioural psychological approach that focuses on confronting alcohol cues in order to reduce cravings as well as the likelihood of relapsing. During CET, individuals are exposed to alcohol-related stimuli whilst their usual drink responses are prevented. Thus, by applying CET during the treatment course, patients are given an opportunity to practise coping strategies when exposed to alcohol in vivo before they are discharged from the treatment system. It is hypothesized that in this way the individual’s conditioned automatic responses will gradually extinguish over time, and that their cognitive control over cue reactivity will strengthen.

Because psychological treatment such as CET is a substantial socio-economic burden when delivered in individual sessions, the trend is towards delivering treatment through group sessions. Mental healthcare applications such as smartphone apps may have even greater potential, both in terms of cost-reduction in the healthcare system and by increasing the availability of evidence-based treatment [9]. However, whilst group sessions have been documented as effective (e.g. [6, 10]), behavioural healthcare apps targeting AUD need further exploration, despite promising preliminary results [11, 12].

### Aims

The aims of the study are:To investigate whether manual-based CET delivered via a smartphone or in group sessions increases the effect of outpatient CBT treatment in AUD individualsTo investigate whether CET as a smartphone application is as effective as CET group aftercare and Aftercare as UsualTo investigate whether CET as a smartphone application is more cost-effective than CET group aftercare and Aftercare as Usual

## Design and methods

The study will be implemented as a parallel investigator-blinded randomized controlled trial. Randomisation occurs by means of computerized urn randomization. The random allocation sequence is generated by a statistician who has no contact with either patients or research assistants. As illustrated below in Fig. 1: Flowchart, a total of 300 consecutively enrolled AUD individuals will be recruited from an alcohol outpatient clinic after concluding a 3-month standard outpatient treatment course. The standard outpatient treatment course typically consists of eight sessions, and is based on cognitive behavioural therapy. The treatment course is planned together with the patient, and the therapy typically consists of psycho-education, functional analysis of drinking situations, development of coping strategies (e.g. waiting out till the urge passes, thinking about the negative consequences of drinking, thinking about positive consequences of sobriety, and intake of alternative food and beverage), problem-solving and homework between sessions.

**Fig. 1 Fig1:**
[figure not shown]
Flowchart

In the present study the patient will be briefly informed about the aftercare project in the second-last session of the standard 3-month outpatient treatment course, and asked if he/she is willing to meet with a research assistant who will provide further information. If so, the patient is informed by the research assistant about this study’s aftercare project right after treatment conclusion. After informed consent, the baseline interview will be carried out, and patients fulfilling the inclusion/exclusion criteria will be randomized into one of the three aftercare treatment groups mentioned below by the means of a computer program. The inclusion criteria are as follows: patients must 1) accept participation in the study and sign written informed consent; 2) be aged between 18 and 60 years, and 3) have completed primary treatment. The exclusion criteria are: 4) patients who are not Danish speakers; 5) patients with acute psychotic disorders or severe cognitive impairment, and 6) patients with terminal somatic illness. Patients fulfilling the above criteria will be randomized into one of the three following aftercare treatment groups: (A) CET as a smartphone application (*n* = 100); (B) CET as group therapy (*n* = 100), and (C) Aftercare as Usual (*n* = 100). Patients in group (A) are encouraged to use the smartphone application four times a week for 8 weeks (a maximum of 36 sessions of approximately 15 min). Patients in group (B) are required to turn up for CET group therapy every other week for 8 weeks (four sessions of 120 min each, with a maximum of eight patients in each group). Patients in group (C) will receive 1 individual follow-up session 8 weeks after discharge from CBT.

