### Statistical analyses

The primary outcome measure is alcohol consumption, comprising a number of drinking variables such as abstinence and controlled drinking. In Denmark, sensible drinking, defined by the Danish Board of Health as ≤ 14 drinks per week for women and ≤ 21 drinks^2^ per week for men, is the most common measure of abstinence or controlled drinking. Therefore we have selected sensible drinking as our primary outcome (26 weeks after baseline assessment). Because no similar study has been conducted using this variable, the power calculation is estimated from quality assurance data and research data from an alcohol outpatient clinic.

Currently, 26 weeks after starting treatment in the current treatment regime, 65 % of the patients have sensible drinking habits (Data from Alkoholbehandlingen i Odense, 2011). In order to detect an effect by comparing the three groups, a sample of 100 patients in each group is needed to have 90 % power of detecting a difference corresponding to an improvement of 18 percentage points using a 5 % level of statistical significance.

The primary and secondary outcome data will be analysed by repeated measures and mixed models in order to detect differences within and between the three groups. The significance level is set at 5 %, and either one-sided or two-sided analyses will be applied depending on the hypothesis being modelled (i.e. a priori or post-hoc). Effect sizes will be reported in accordance with the statistical modelling. For each outcome measure, two analyses will be carried out: 1) multiple imputation analyses will be carried out for all patients, irrespective of whether they have completed the interventions or were re-interviewed. 2). Completer (on-treatment) analyses will be carried out for patients who have completed the respective interventions.

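### Only the group-CET arm is delivered in therapy groups, yet the sample size makes no allowance for this and the stated analysis names no therapy-group term; if none is fitted and outcomes correlate within groups, standard errors for B v C and A v B will be too small

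*Protocol article*

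**What the plan says.** The Design and methods section of the protocol article (paragraph below Fig. 1) randomises patients individually to three arms of 100. Arm B attends CET every other week for 8 weeks: "four sessions of 120 min each, with a maximum of eight patients in each group". Arm A works alone with the app, and arm C has one individual follow-up session.

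The Statistical analyses section sets the primary outcome as sensible drinking at 26 weeks, a yes/no variable. For the sample size it takes a current rate at which "65 % of the patients have sensible drinking habits" and states that "a sample of 100 patients in each group is needed to have 90 % power". The effect to be found is "a difference corresponding to an improvement of 18 percentage points", tested at the 5% significance level. It gives no ICC, design effect or group-size allowance.

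The outcomes are to be "analysed by repeated measures and mixed models in order to detect differences within and between the three groups". In that sentence the groups are the three arms. The random effects are not listed, and the article nowhere mentions therapy groups as a source of correlation. On sidedness, "either one-sided or two-sided analyses will be applied depending on the hypothesis being modelled".

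**The concern.** This is an individually randomised, partially nested design: one arm is clustered after randomisation and two are not. Members of a therapy group go through the same sessions and exposure exercises with the same peers for 8 weeks, so some correlation in their later drinking is plausible. A patient-level random effect for repeated measures does not absorb variation between therapy groups.

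Two separate consequences follow. The sample-size omission means that B v C power is lower than stated. An analysis without a therapy-group term would give intervals that are too narrow and too many false positives in B v C and A v B. The second contrast matters because the Aims section asks whether the app is as effective as group CET, and an interval that is too narrow makes a claim of similarity too easy as well as a claim of difference.

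**Working it through.** **Inputs from the protocol article.** Control rate 0.65; improvement 0.18, so 0.83; 5% level; 90% power; 100 per arm (Statistical analyses). Group size m at most 8 in arm B (Design and methods). Number of therapy groups: 100/8 = 12.5, so at least 13.

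**Assumption.** The ICC is not in the document; 0.01, 0.05 and 0.10 are used as a range.

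**Step 1: reproduce the stated sample size.** With mean rate 0.74, 2 × 0.74 × 0.26 = 0.3848 and 0.65 × 0.35 + 0.83 × 0.17 = 0.3686.

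n = [z_α √0.3848 + 1.2816 √0.3686]² / 0.18²

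- One-sided (z_α = 1.645): (1.020 + 0.778)² / 0.0324 = 99.8, so 100. This matches exactly.
- Two-sided (z_α = 1.960): (1.216 + 0.778)² / 0.0324 = 122.7, so 123. At 100 per arm the two-sided power is 83.2%.

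The 100 is used up by the independent-patients formula one-sided and falls short of it two-sided. Neither version leaves room for a design effect.

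**Step 2: formulas with clustering in arm B only.**

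- Design effect: DE = 1 + (m − 1) × ICC. Effective n in arm B = 100/DE.
- If therapy group is ignored, the true standard error under the null exceeds the reported one by f = √[(1 + DE)/2].
- True two-sided error = 2[1 − Φ(1.96/f)]; one-sided = 1 − Φ(1.645/f).
- B v C power with the clustering accounted for = Φ[(0.18 − z_α SE₀)/SE₁], where SE₀² = 0.1924(DE + 1)/100 and SE₁² = (0.1411 DE + 0.2275)/100.

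Example, m = 8 and ICC 0.05: DE = 1 + 7 × 0.05 = 1.35; f = √1.175 = 1.084; SE₀ = 0.0672; SE₁ = 0.0647; two-sided power = Φ[(0.18 − 1.96 × 0.0672)/0.0647] = 77.2%.

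**Step 3: results.**

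| m | ICC (assumed) | DE | Effective n in B | f | Error, two-sided | Error, one-sided | B v C power, one-sided | B v C power, two-sided |
|---|---|---|---|---|---|---|---|---|
| any | 0 | 1.00 | 100 | 1.000 | 5.0% | 5.0% | 90.0% | 83.2% |
| 8 | 0.01 | 1.07 | 93.5 | 1.017 | 5.4% | 5.3% | 89.2% | 82.0% |
| 8 | 0.05 | 1.35 | 74.1 | 1.084 | 7.1% | 6.5% | 85.8% | 77.2% |
| 8 | 0.10 | 1.70 | 58.8 | 1.162 | 9.2% | 7.8% | 81.6% | 71.5% |
| 4 | 0.01 | 1.03 | 97.1 | 1.007 | 5.2% | 5.1% | 89.7% | 82.7% |
| 4 | 0.05 | 1.15 | 87.0 | 1.037 | 5.9% | 5.6% | 88.3% | 80.6% |
| 4 | 0.10 | 1.30 | 76.9 | 1.072 | 6.8% | 6.3% | 86.5% | 78.1% |

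The error columns apply equally to A v B, because arm A is also unclustered.

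**The case against.** The strongest objection is that a condensed article need not list random effects. A mixed model can carry a therapy-group term, and the full protocol or SAP, not shown here, may specify one. That stands against any flat statement that the analysis ignores clustering. It does not answer the sample-size point, where the article gives a complete calculation that leaves clustering out.

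A reader might infer several stronger things that the document does not support:

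- *That the standard errors are too small as a matter of fact.* This needs both a positive ICC and a final model without a therapy-group term. The article establishes neither.
- *That the sample-size omission itself shrinks standard errors.* It costs power; only the analysis can understate the variance.
- *That the omission biases results towards group CET.* The point estimate is not shifted. False positives rise in both directions.
- *That two-sided power with clustering should be set against the stated 90%.* Most or much of that gap is sidedness. At ICC 0.05 and m = 8, the drop from 90.0% to 83.2% comes from moving to a two-sided test, and only the drop from 83.2% to 77.2% from clustering.
- *That patients in a group share one therapist, or that groups are closed.* The article says neither, and enrolment is consecutive, so groups may be rolling.

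The size may also be small. Eight is a maximum, and the primary endpoint falls 26 − 8 = 18 weeks after the groups end, so the correlation may have weakened by then.

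**Conclusion.** The point holds in conditional form. It is certain that arm B alone is delivered in groups and that the stated 90% power treats its patients as independent. It is conditional that standard errors for B v C and A v B will be too small: that requires a positive ICC and no therapy-group term in the fitted model. The article neither names such a term nor rules it out. A v C is unaffected.

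Under the assumed ICCs, the effect is slight at 0.01 and becomes material at about 0.05 to 0.10 with full groups. The figures for eight per group are upper bounds for each ICC. They rest on a normal approximation, and the power figures on the pooled-variance formula. This should be corrected because it is cheap, but it does not undermine the trial.

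**What to change.** 1. Record which therapy group each arm-B patient attended, session by session. If membership is not captured, no later analysis plan can recover it.
2. State that the mixed model is partially nested: a therapy-group random effect in arm B only, with patients in A and C unclustered, and small-sample degrees of freedom because there may be only about 13 groups. If groups are rolling, adapt the term to overlapping membership, for example with a multiple-membership structure.
3. Include therapy group in the arm-B imputation model, so that the multiple-imputation analysis keeps the same correlation.
4. Restate B v C power over a stated ICC range and for the sidedness actually intended. No extra enrolment is needed for this; the aim is an honest power statement.

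The cost is one membership variable, one random term and a short paragraph on power. The downside is slightly wider intervals for comparisons involving arm B.

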### CET aftercare

CET is most commonly used in combination with various urge-specific coping strategies (USCS) because this has been shown to provide better treatment outcomes [13, 14]. In this study, we will apply the treatment manual for CET with USCS recommended by Monti and colleagues [14], which emphasizes the importance of patients being confronted with alcohol in order for cue reactivity to diminish. During each CET session, the patient is introduced/reintroduced^1^ to effective USCS and afterwards required to practise the strategies learned whilst being exposed in vivo to alcohol. The recommended strategies are as follows: 1) waiting it out; 2) thinking about the negative consequences of drinking; 3) thinking about the positive consequences of sobriety, and 4) alternative food and beverage intake. In a recent study, negative consequences of drinking and positive consequences of sobriety were identified as the most effective USCS related to treatment outcome among 13 such strategies, whereas alternative food and beverage intake was surprisingly not even significantly related [15]. However, other studies have reported good effects for all of them [10, 16, 17], and further research would be needed to exclude any of them from the CET treatment program. Both experimental groups, (A) and (B), will receive manual-based CET since CET is suitable for individual as well as group therapy.

#### CET aftercare via a smartphone application

Based on the Monti et al. [14] manual, CET is provided in some treatment programmes in Danish alcohol clinics in both outpatient and inpatient treatment settings. Due to the structure of the treatment and clinical experience with the method, we have been able to transform the method into a smartphone application (Fig. 2). The application is individually adaptive in terms of the contents of USCS as well as the alcohol exposure material.

**Fig. 2 Fig2:**
[figure not shown]
Smartphone app illustration

The exposure to alcohol is simulated by watching one of ten alcohol videos on the smartphone (beer, red or white wine, mixed alcoholic drinks, hard liquor etc.…), which allows the patient to select his/her preferred beverage as exposure material. The alcohol exposure videos imitate sessions with a therapist, and the alcohol presented in the videos becomes increasingly appetitive during the exposure session, in order to induce cue controlled cravings. The application contains a direct number to a CET therapist in case of uncontrollable cravings, and the app is only accessible during the opening hours of the alcohol outpatient clinic (Monday to Friday from 9 to 18). Patients are able to practise exposure once a day, four times a week, and they are sent a reminder by text message from the software 4 times a week. Exposure activities as well as effectiveness will be measured by algorithms of cravings during exposure, coupled to a data-monitoring system.

The application has the advantage of allowing patients to practise exposure at home and in a variety of real-life situations. Compared to the CET treatment delivered in alcohol clinics, this approach may increase the likelihood that the extinction learning will generalize to various other contexts outside the usual treatment setting.

#### Aftercare as usual

The usual aftercare consists of a single follow-up session, during which the patient is asked how he/she is doing and, if needed, offered a brush-up of the coping strategies.

### Measures

Demographic data are recorded for all patients when entering alcohol treatment. Assessment for harmful use and dependence on alcohol by means of the ICD-10 Diagnostic Criteria for Research (DCR-10) and the Addiction Severity Index (ASI) also forms part of the routine clinical assessment and is carried out for all patients when entering primary treatment, and at conclusion. Typically, more than 90 % of the patients suffer from alcohol dependence at treatment entry (Data from Alkoholbehandlingen i Odense, 2011).

Patients suffering from severe dementia or acute psychosis are not offered treatment at the outpatient clinic but referred elsewhere. At the conclusion of the primary treatment and before randomization, patients fulfilling the exclusion/inclusion criteria will be further assessed by means of the primary and secondary treatment outcomes in order to be able to measure the effect of the CET aftercare treatment. The primary and secondary outcome measures are presented in Table 1: Measurements.

**Table 1 Tab1:** Measures

Domain	Measure	Content	Reference	Time-point
Primary outcome				
Alcohol consumption	Timeline Followback (TLFB)	TLFB is used to identify alcohol-free days as well as number of drinks per day. Patients indicate their daily standard drink intake before administration.	[26]	Baseline and follow-up (after 8 and 26 weeks)
Secondary outcomes				
Addiction severity	Addiction Severity Index (ASI)	ASI assesses characteristics and problems in various domains of life; e.g. alcohol and drug use module – and also physical and mental health, employment, legal problems and social functioning.	[27]	Baseline and follow-up (after 8 and 26 weeks)
Craving	Desires for Alcohol Questionnaire (DAQ)	DAQ measures three dimensions of current craving: desire and intention to use alcohol; negative reinforcement of alcohol use, and control of alcohol use.	[28]	Baseline and follow-up (after 8 and 26 weeks)
	Obsessive Compulsive Drinking Scale (OCDS)	The OCDS is designed to reflect obsessive patterns and compulsivity related to craving and drinking behaviour.	[29]	Baseline and follow-up (after 8 and 26 weeks)
	The Visual Analogue Scale for Craving (VAS)	VAS measures on the subjective experience of the intensity of current craving for alcohol.	[30]	Baseline and follow-up (after 8 and 26 weeks)
Coping skills and self-efficacy	The Urge-Specific Strategies Questionnaire (USS)	USS is designed to assess the patient’s use of coping skills when trying to stop themselves from drinking after experiencing an urge.	[14]	Baseline and follow-up (after 8 and 26 weeks)
	Alcohol Abstinence Self-Efficacy Scale (AASE)	The AASE assesses self-efficacy and evaluates an individual’s efficacy (e.g. confidence in their ability) to abstain from drinking.	[31]	Baseline and follow-up (after 8 and 26 weeks)

Data will be collected at three different points in time: T_0,_ the baseline (which in this case is after conclusion of treatment, but before entering aftercare); T_1,_ after having completed aftercare treatment, 8 weeks after the baseline assessment, and T_2,_ 26 weeks after baseline. T_2_ is the primary time endpoint.

In addition to the measurements 8 and 26 weeks after CET aftercare or control group, patients will be followed up 1 year after concluding aftercare treatment through the following population registers: The Danish National Patient Register [18], 2011), The Danish National Health Service Register [19], The Danish National Prescription Registry [20] and The Danish Psychiatric Central Research Register [21]. The registers provide data about contact to the healthcare system as well as reason for contact and prescriptions during the period, which will enable us to detect relapses.

The cost-effectiveness of CET by smartphone intervention will be compared by healthcare expenditure per primary outcome unit in group (A) versus groups (B) and (C). Healthcare expenditure is measured according to the international Classification of Health Accounts [22], and almost all components can be extracted from the above-mentioned population registers.

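### Cost-effectiveness is stated as expenditure per outcome unit by group, an average ratio whose ranking can shift with healthcare spending common to all arms and so may not answer the third aim

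*Protocol article*

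**What the plan says.** The third aim (protocol article, Aims) is to find out whether "CET as a smartphone application is more cost-effective than CET group aftercare and Aftercare as Usual". The Measures section gives the only method for it: cost-effectiveness "will be compared by healthcare expenditure per primary outcome unit in group (A) versus groups (B) and (C)". It adds that expenditure follows an international classification of health accounts and that "almost all components can be extracted from the above-mentioned population registers". The four registers named there cover healthcare contacts, the reasons for contact and prescriptions in general. Nothing restricts the expenditure to aftercare or to alcohol-related care.

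The outcome unit comes from Statistical analyses: "Therefore we have selected sensible drinking as our primary outcome (26 weeks after baseline assessment)". The same section supplies the planning rates. Under the current regime "65 % of the patients have sensible drinking habits", and the trial is sized for "a difference corresponding to an improvement of 18 percentage points".

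The article does not mention incremental cost, incremental effect, net benefit or a willingness-to-pay value.

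**The concern.** An average ratio divides everything spent in an arm by every good outcome in it. The arm is credited with patients who would have been sensible drinkers under usual aftercare, and charged with care that has nothing to do with aftercare. Whether the app is more cost-effective than a comparator depends instead on what it adds: extra cost against extra effect.

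The two approaches can part company when one arm is both more effective and costlier. That is a realistic outcome here. Against usual aftercare, which is a single follow-up session, the app offers up to 36 sessions and a direct line to a therapist, so better at higher cost is a result that the trial might well find. Against group sessions, the app might prove cheaper but somewhat less effective. In either case the ranking by average ratio depends partly on the general level of healthcare spending in the population, which the aftercare does not set. The Discussion looks to the app to reduce the burden on the healthcare system, so the ranking would be used.

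**Working it through.** **Plan's own figures.** The article states no cost and no cost-effectiveness result, so there is nothing of that kind to reproduce. The rates used below are its own: pC = 0.65 and pA = 0.65 + 0.18 = 0.83. Reading the 18 points this way is consistent with its sample size: 65 % v 83 % with 90 % power and a one-sided 5 % test gives 100 per group, as stated. A two-sided test would need 123, but that is a separate matter.

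**Assumptions.** The outcome unit is one patient with sensible drinking at 26 weeks. All costs are assumed, in arbitrary currency units, because the article gives none.

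**Formulas.** Let cA and cC be mean cost per patient, and K a further amount spent on every patient in both arms.

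- Average ratio: (K + c)/p in each arm.
- Incremental ratio: (cA − cC)/(pA − pC). K cancels.
- The average-ratio ranking changes at K* = (pC·cA − pA·cC)/(pA − pC).

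**A v C, with cA = 13,000 and cC = 10,000.**

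| K | C | A | Lower | Incremental |
|---|---|---|---|---|
| 0 | 10,000/0.65 = 15,385 | 13,000/0.83 = 15,663 | C | 3,000/0.18 = 16,667 |
| 5,000 | 15,000/0.65 = 23,077 | 18,000/0.83 = 21,687 | A | 3,000/0.18 = 16,667 |

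Here K* = (0.65 × 13,000 − 0.83 × 10,000)/0.18 = 150/0.18 = 833.

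**Why it happens.** With pA > pC, the condition (K + cA)/pA < (K + cC)/pC rearranges to (cA − cC)/(pA − pC) < (K + cC)/pC. So A ranks first exactly when its incremental ratio lies below the comparator's average ratio. In effect, the comparator's average spend per sensible drinker becomes the willingness-to-pay threshold. In the table, 16,667 is compared with 15,385 in the first row and with 23,077 in the second.

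**A v C, aftercare cost separated from background spend (cA = 3,000, cC = 500).** K* = (0.65 × 3,000 − 0.83 × 500)/0.18 = 1,535/0.18 = 8,528. At K = 5,000 the ratios are 8,462 (C) and 9,639 (A), so C is lower. At K = 9,000 they are 14,615 and 14,458, so A is lower. The incremental ratio is 2,500/0.18 = 13,889 throughout. With cC = 500 and an extra aftercare cost of 1,000 to 5,000, K* runs from 3,111 to 17,556.

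**A v B, app cheaper and less effective (costs 500 v 2,000, and 0.70 v 0.83 assumed).** K* = (0.70 × 2,000 − 0.83 × 500)/0.13 = 985/0.13 = 7,577. At K = 7,500 the ratios are 11,429 (A) and 11,446 (B), so A is lower. At K = 8,000 they are 12,143 and 12,048, so B is lower. The incremental ratio is 1,500/0.13 = 11,538 throughout. With 0.78 in place of 0.70, K* is 22,900.

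**Where no change occurs.** If A costs less and its proportion is at least as high, A has the lower average ratio at every K and is also preferred incrementally.

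**The case against.** The strongest reply is that this is one compressed sentence in a journal article. Setting group A against groups B and C could be shorthand for a between-arm, incremental comparison. The article gives no formula, and the full protocol or a health-economic plan, neither of which is shown, may specify one. That limits how firmly the point can be pressed. It does not remove it, because the sentence names a metric instead of leaving one open, and the natural reading of that metric is a ratio within each group.

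It is also fair to say that the illustration does not show a wrong answer. An incremental ratio of 16,667 favours neither arm until a threshold is set, and the first scenario lies close to the point of change. Nor is it a fault in itself that a cheaper, less effective arm comes out ahead: incremental analysis also prefers such an arm when willingness to pay is low enough. And the article expects the app to save cost and asks whether it is as effective as group sessions; if both are borne out, the A v B ranking is safe. All of this stands. What the arithmetic shows is that the ranking depends on spending unrelated to the comparison.

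Two stronger readings are tempting, and the article supports neither.

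- *A mismatch of periods.* A reader might note that "patients will be followed up 1 year after concluding aftercare treatment through the following population registers", about 8 + 52 = 60 weeks from baseline, while the outcome is at 26 weeks. But the purpose that the article gives for that follow-up is to detect relapses. It states no costing period, and does not say that one-year costs will be divided by a 26-week outcome.
- *Missing delivery costs.* A reader might infer that the cost of delivering the app and the groups is left out. The article says only that nearly all components can come from registers, which leaves room for the rest to come from elsewhere.

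**Conclusion.** The point holds in a limited form. As written, the comparison is of average cost-effectiveness ratios by arm, which suits a comparative aim badly. When the more effective arm is also the costlier one, healthcare spending common to the arms can change the ranking while the incremental result stays put: 15,385 v 15,663 becomes 23,077 v 21,687, against 16,667 in both cases. The size rests on assumed costs and on the planning rates of 65 % and 83 %; it shows that a change can occur, not that it will. It would be too strong to say that the third aim will be answered in the wrong direction. The ranking may simply fail to answer it. Confidence is moderate, because the text is one condensed sentence. The primary efficacy analysis, the sample size and the data collection are unaffected.

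**What to change.** Replace the sentence in Measures, or override it in the analysis plan before costs and outcomes are examined together, with wording such as:

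> For A v B and A v C, the difference in mean healthcare cost and the difference in the proportion with sensible drinking are estimated over a stated common period and reported as an incremental cost-effectiveness ratio or net benefit with confidence intervals.

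The choice of period is a trade-off for the investigators. A shorter one matches the primary endpoint; a longer one takes in later relapse-related costs. It should be named in advance. If a fuller plan already specifies an incremental analysis, the article's sentence only needs to be brought into line with it.

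The cost is analysis wording and a little more analysis of data already planned. No new patients, visits or measurements are needed.
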